### Withdrawal and Urge Questions

1. On a scale from 1 to 10, how strong have your urges to smoke been over the last week?
- |                      |                      |
|----------------------|----------------------|
| 1. Not at all strong | 6.                   |
| 2.                   | 7.                   |
| 3. A little strong   | 8. Very strong       |
| 4.                   | 9.                   |
| 5. Moderately strong | 10. Extremely strong |

2. On a scale from 1-10, how bad have your withdrawal symptoms (for example, irritability or agitation that occur when you don't smoke) been over the last week?

- |                        |                        |
|------------------------|------------------------|
| 1. Not at all stressed | 6.                     |
| 2.                     | 7.                     |
| 3. A little stressed   | 8. Very stressed       |
| 4.                     | 9.                     |
| 5. Moderately stressed | 10. Extremely stressed |

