#### Exploratory Objectives

6. To assess potential baseline (pre-intervention) predictors of abstinence including self-reported dependence, stress, anxiety, depression, alcohol and drug use, and self-efficacy. If a baseline variable is found to be associated with abstinence, it will be further assessed as a moderator of abstinence.
7. To assess change in self-reported measures at baseline (pre-quit) to 2- and 12-weeks post TQD on repeated standardized measures of nicotine dependence, stress, anxiety, depression, alcohol and drug use, and self-efficacy. If a measure is found to change significantly from baseline to a post quit time point, it will be assessed as possible mediator of abstinence outcomes.
8. To compare phone-assessed non-standardized single item questions on urges, withdrawal, motivation to quit smoking or remain abstinent, and confidence in ability to quit or remain abstinent at 1, 2, 6, 12, 26 and 52 weeks post-TQD. If a measure is found to change significantly from baseline to a post quit time point, it will be assessed as a possible mediator of abstinence outcomes. Phone assessments will be compared at specific time points and also across multiple time points using multi-level modeling.

9. To compare baseline scores on anxiety, depression, and stress for their effect on allocation to Responder or Non-Responder status in the adaptive and standard treatment arms.
10. To conduct cost-benefit analyses on allocation to adaptive vs standard treatment from the perspective of multiple stake holders: smokers, healthcare systems (clinics/hospitals), insurance companies, and employers.

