### **Confidence in Ability and Motivation to Become Tobacco-Free**

1. On a scale of 1-10, how motivated are you to quit smoking or stay quit if abstinent?

- |                         |                         |
|-------------------------|-------------------------|
| 1. Not at all motivated | 6.                      |
| 2.                      | 7.                      |
| 3. A little motivated   | 8. Very motivated       |
| 4.                      | 9.                      |
| 5. Moderately motivated | 10. Extremely motivated |

2. On a scale of 1-10, how confident are you that you can quit if abstinent or stay quit if abstinent?

- |                         |                         |
|-------------------------|-------------------------|
| 1. Not at all confident | 6.                      |
| 2.                      | 7.                      |
| 3. A little confident   | 8. Very confident       |
| 4.                      | 9.                      |
| 5. Moderately confident | 10. Extremely confident |

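### The phone withdrawal item is answered on a scale labelled for stress, so its score is ambiguous; the confidence item and the Section 10.7.6 list also need correcting (exploratory analyses only)

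*Protocol*

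**What the plan says.** Exploratory objective 8 (protocol Section 3.1, repeated in the Section 6 table) sets out to compare "phone-assessed non-standardized single item questions on urges, withdrawal, motivation to quit smoking or remain abstinent", together with confidence, at weeks 1, 2, 6, 12, 26 and 52 after the target quit day. An item that changes significantly from baseline is to be examined as a possible mediator of abstinence. Exploratory hypothesis 8 names the same four constructs as predictors of phone-reported abstinence.

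The questions are printed in Appendix 19. The withdrawal question reads "how bad have your withdrawal symptoms (for example, irritability or agitation that occur when you don't smoke) been over the last week". Its scale starts at "Not at all stressed" and ends at "Extremely stressed". The confidence question asks how sure the participant is that "you can quit if abstinent or stay quit if abstinent".

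Section 10.7.6 lists what is collected by phone and points to Appendix 19 for the questions. The list covers abstinence status, cigarettes per day, medications with side effects, stress, urges and confidence. Withdrawal and motivation are not on it.

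**The concern.** A single-item measure has nothing but its stem and its anchors to define it. Here they name different things. Someone with few withdrawal symptoms but a hard week at work could reasonably give a high number by following the labels, or a low one by following the question. The protocol treats stress as a separate predictor and candidate mediator, so a withdrawal score given in stress terms blurs two constructs that it means to keep apart.

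At stake is what objective 8 can say about withdrawal over time, and whether any mediation finding from the item could be attributed to withdrawal. The confidence wording and the mismatch between Section 10.7.6 and Appendix 19 raise the same worry on a smaller scale: the form and the text do not agree on what is being measured.

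**Working it through.** No formula applies. The check sets the form, the section that describes it and the objectives that use it side by side.

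**1. Stem against anchors, Appendix 19**

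| Phone item | Stem asks about | Lowest anchor | Match? |
|---|---|---|---|
| Urges | strength of urges | "Not at all strong" | yes |
| Withdrawal | how bad symptoms were | "Not at all stressed" | **no** |
| Motivation | how motivated | "Not at all motivated" | yes |
| Confidence | how confident | labelled in terms of confidence | yes |

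On the withdrawal item the labelled points are 1, 3, 5, 8 and 10. All 5 of 5 are stress labels and none refers to withdrawal. The other three items follow one pattern, so this is a slip in one item and not a convention of the form. The two questions in the block are numbered 1 and 2 in order under a heading that names withdrawal and urges, and nothing suggests that a separate stress question was lost in text extraction.

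**2. Constructs listed against constructs asked and needed**

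| Construct | Section 10.7.6 | Question in Appendix 19 | Needed by objective 8 |
|---|---|---|---|
| Urges | listed | yes | yes |
| Withdrawal | not listed | yes, wrong anchors | yes |
| Motivation | not listed | yes | yes |
| Confidence | listed | yes, garbled stem | yes |
| Stress | listed | none | no |

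The mismatch runs both ways: one construct is promised without a question, and two are asked and needed without being listed.

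**3. Is there a substitute for the withdrawal item?** Section 10.7.5 says that the MPSS-2 captures withdrawal at clinic visits. As printed in Appendix 15 it has two questions, on the frequency and the strength of urges, and Sections 3.6 and 13.5.1 themselves describe the MPSS as an urge rating. On the printed forms, the phone item is the only question that asks for an overall rating of withdrawal symptoms.

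**4. The confidence stem.** Both of its branches depend on abstinence. The motivation item directly above it asks about quitting, or about staying quit for those already abstinent. Objective 8 likewise means confidence in quitting or in remaining abstinent. The first condition in the confidence stem looks like a duplication.

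**5. Reach.** Objective 8 names six time points, which correspond to calls 5 to 10 in the Section 10.4 timetable, or 6 of the 10 calls. Appendix 19 does not assign call numbers to these items, so any other calls that carry them cannot be counted from the document.

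**The case against.** The strongest reply is that the withdrawal stem is clear. It names the symptoms, gives examples, sets a one-week window, asks for a number and sits under a matching heading. Many participants will answer what was asked. The same form is used in both arms of a blinded trial, so the labels have no evident direction in favour of either arm. Nor is the item in the mediator lists of Sections 3.6 and 13.5.1; it reaches mediation only through the conditional clause in objective 8.

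All of that stands, and it limits the consequence. It does not remove the ambiguity, because using the same form in both arms does not tell the analyst which construct a given score reflects.

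A reader might go further in four ways that the documents do not support:

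- *That withdrawal is not validly measured at all.* The item still carries some information about withdrawal. The documents show that it is ambiguous, not that it is invalid.
- *That a stress endpoint has been lost.* No phone objective names stress. Stress as predictor, moderator or mediator rests on the PSS-4, which is collected at clinic visits. The gap is a disagreement between Section 10.7.6 and Appendix 19.
- *That someone still smoking cannot answer the confidence item.* Most could guess the intended question from the item above it. The wording is garbled, but there is no evidence of how smokers would respond.
- *That a phone stress question must be added.* Removing stress from the list reconciles the text equally well.

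**Conclusion.** The point holds in a narrow form. The phone withdrawal item pairs a withdrawal question with stress labels at every labelled point, so its score is ambiguous between the two. No other printed question replaces it. The confidence item contains a wording slip, and Section 10.7.6 and Appendix 19 list different phone constructs.

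The size is small. What is affected is exploratory objective 8, exploratory hypothesis 8 so far as it draws on these items, and any mediator analysis that follows from the objective. Abstinence and cigarettes per day come from separate questions, so the primary and secondary outcomes are unaffected.

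The conclusion assumes that the forms printed in the appendices are the ones used on the calls and at the visits. If the REDCap version already carries corrected anchors, only the printed text needs changing. The point is still worth acting on because the ambiguity enters when the answer is given, and no later analysis can separate the two readings.

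**What to change.** - **Withdrawal item:** replace the stress labels with severity labels that match the stem, from *not at all bad* to *extremely bad*, keeping the 1-10 scale.
- **Confidence item:** follow the motivation item, so that the first branch is *quit smoking* and the second is *stay quit if abstinent*.
- **Section 10.7.6:** add withdrawal and motivation. Then either delete stress from the list or add a phone stress question to Appendix 19. Either choice is consistent with the objectives; the first adds no burden, the second adds one short question per call.

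The cost is a form and REDCap edit. If calls have already begun, record which form version each call used, report withdrawal scores from the old version as ambiguous, and do not carry them forward as a withdrawal mediator without that caveat.

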### **Confidence in Ability and Motivation to Become Tobacco-Free**

1. On a scale of 1-10, how motivated are you to quit smoking or stay quit if abstinent?

- |                         |                         |
|-------------------------|-------------------------|
| 1. Not at all motivated | 6.                      |
| 2.                      | 7.                      |
| 3. A little motivated   | 8. Very motivated       |
| 4.                      | 9.                      |
| 5. Moderately motivated | 10. Extremely motivated |

2. On a scale of 1-10, how confident are you that you can quit if abstinent or stay quit if abstinent?

- |                         |                         |
|-------------------------|-------------------------|
| 1. Not at all confident | 6.                      |
| 2.                      | 7.                      |
| 3. A little confident   | 8. Very confident       |
| 4.                      | 9.                      |
| 5. Moderately confident | 10. Extremely confident |

### **26- and 52-Week Call Questions**

1. Since completing your last visit with us, have you used any smoking cessation medications? (Nicotine patches, gum/lozenge, inhaler, Chantix, Wellbutrin, bupropion, or Zyban) Yes    No

2. Since completing your last visit with us, have you smoked at all, even a puff? Yes    No

## Appendix 20: 7 Day Smoking History and Medication Adherence Diary

Please record your medication use and smoking each day, starting seven days before your next visit.

(Will be adjusted based on medication regimen chosen and specific in-person visit)

|                   | Date      | # cigs smoked? | Did you take your Chantix pills today?                    |                                                                  | Did you take your Bupropion/placebo pills today?          |                                                                  |
|-------------------|-----------|----------------|------------------------------------------------------------------|------------------------------------------------------------------|------------------------------------------------------------------|------------------------------------------------------------------|
|                   |           |                | First Dose                                                       | Second Dose                                                      | First Dose                                                       | Second Dose                                                      |
| 1          | ____/____ | _____          | Pill 1:
 YES
 NO | Pill 2:
 YES
 NO | Pill 1: 
YES 
NO | Pill 2: 
YES 
NO |
| 2          | ____/____ | _____          | Pill 1:
 YES
 NO | Pill 2: 
YES 
NO | Pill 1: 
YES 
NO | Pill 2: 
YES 
NO |
| 3          | ____/____ | _____          | Pill 1:
 YES
 NO | Pill 2: 
YES 
NO | Pill 1: 
YES 
NO | Pill 2: 
YES 
NO |
| 4          | ____/____ | _____          | Pill 1:
 YES
 NO | Pill 2: 
YES 
NO | Pill 1: 
YES 
NO | Pill 2: 
YES 
NO |
| 5          | ____/____ | _____          | Pill 1:
 YES
 NO | Pill 2: 
YES 
NO | Pill 1: 
YES 
NO | Pill 2: 
YES 
NO |
| 6          | ____/____ | _____          | Pill 1:
 YES
 NO | Pill 2: 
YES 
NO | Pill 1: 
YES 
NO | Pill 2: 
YES 
NO |
| 7          | ____/____ | _____          | Pill 1:
 YES
 NO | Pill 2: 
YES 
NO | Pill 1: 
YES 
NO | Pill 2: 
YES 
NO |
| Next Visit | ____/____ |                |                                                                  |                                                                  |                                                                  |                                                                  |
